### Recruitment {15}

All individuals who have donated blood in one of NHSBT’s blood donation sessions during the trial period have been included in the trial, unless they opted out using the procedure described above.

## Assignment of interventions: allocation

### Sequence generation {16a}

Randomisation of donation sites (“clusters”) to intervention sequences has been undertaken at the trial’s academic coordinating centre, using a computer program written to implement a previously described method for sequential treatment assignment, balancing for known prognostic factors [26]. Specifically, the program implemented a restricted randomisation procedure [27], ensuring that differences in the following key prognostic characteristics at baseline across the assigned intervention groups remained within predefined tolerance limits: historical VVR rates; total number donors bled; and type of site (i.e. static centre or mobile team). Acceptable randomisations were required to have <10% maximal differences in means of continuous characteristics and a maximal difference of 1 in the sum of binary characteristics between any two intervention groups. No stratification was applied in the randomisation. Randomisation simulations were run to generate 100 acceptable trial designs, which required running 59,819 simulations (or 0.17% acceptance proportion). The final allocation was made at a public event, during which two members of the trial’s independent patient and public involvement and engagement (PPIE) panel selected from the list of 100 randomly generated acceptable allocations, drawing a number between zero and nine from two urns corresponding to the numbering of the list of acceptable trial designs. The randomisation procedure and the statistical code used have been reviewed by an external independent expert who confirmed its validity.

### Concealment mechanism {16b}

During the study period, only two people (the trial statistician and study coordinator) were aware of the study randomisation. NHSBT teams (clusters) were informed of the upcoming intervention changes approximately 1 week prior to commencement to allow them to order supplies to deliver the interventions. This process was repeated for each 9-month period.

### Implementation {16c}

The trial statistician at the academic coordinating centre generated the allocation sequence at the beginning of the trial. Every 9 months, when the intervention allocations changed, the trial statistician contacted staff at NHSBT to roll out the next phase of interventions.

## Assignment of interventions: blinding

### Who will be blinded {17a}

As noted above, participants and analysts have not been blinded to the interventions they have received.

### Procedure for unblinding if needed {17b}

Not applicable, this trial is not blinded.

## Data collection and management

### Plans for assessment and collection of outcomes {18a}

Via a Secure File Transfer Protocol (SFTP), NHSBT staff have shared pseudonymised information about donors’ demographic characteristics and adverse donation events (including VVRs) with authorised staff at the academic coordinating centre. All data shared have been strictly pseudonymised (i.e. stripped of personal identifiers). To enhance collection of information on relevant trial outcomes, NHSBT staff have sent donors SMS text messages immediately after donation visits, asking them to report any adverse events by phoning the NHSBT Customer Care line. All adverse events reported by the donors will be assessed by a nurse at the time of reporting and if considered serious, the coordinating centre is informed, along with the study Sponsor and ethics committee.

### Plans to promote participant retention and complete follow-up {18b}

Not applicable; this trial does not involve the need for participant retention or follow-up beyond the mechanisms described above.

### Data management {19}

A formal Data Sharing Agreement was agreed between NHSBT and the University of Cambridge, prior to the start of the STRIDES trial. On a daily basis, NHSBT staff have forwarded to an authorised data manager at the academic coordinating centre pseudonymised extracts from NHSBT’s database including information on donors: donation history, attendance and deferrals; adverse events; microbiology results; merged donor records; and the right to be forgotten. Reports have been in .csv format (accessible only to authorised staff) and uploaded to the SFTP site. These daily extracts have been imported into a password-protected restricted access SAS database where the provided anonymous ID (GUID) has been replaced by a separate anonymous study ID; the link table between GUID and study ID has been available only to an authorised data manager at the academic coordinating centre.

Queries are automatically generated by the STRIDES Data Management systems (written in SAS) by cross-checking/looking for inconsistencies in the data. Resulting queries are resolved by the study helpdesk, by either looking things up in NHSBT systems or contacting the participant directly. Once resolved, any updates/corrections are entered into an Access database by the helpdesk. The Access database is then automatically read into the Data Management systems and updates corrections are automatically implemented. The Data Management Team is responsible to review the data and ensure it is clean prior to analyses.

### Plans to give access to the full protocol, participant-level data and statistical code {31c}

Data access requests should be made to [contact].

### Confidentiality {27}

Not applicable; no personal, identifiable information is collected as part of this trial.

### Plans for collection, laboratory evaluation and storage of biological specimens for genetic or molecular analysis in this trial/future use {33}

During the trial period, a subset of donors have been asked if they wish to join the STRIDES/NIHR BioResource – Research Tissue Bank (henceforth, ‘STRIDES BioResource’), in keeping with the trial’s secondary objective to advance understanding of the determinants of VVRs and to help develop prevention strategies for VVRs tailored to specific donor sub-populations, based on demographic, biological, psychosocial, and other characteristics. Donors who consent to participate in the STRIDES BioResource have been asked to provide a 20-ml blood sample (at the session) and to complete online questionnaires (after the session) concerning VVRs and broader health and donation questions. A full blood count has been performed from the collected blood sample using a Sysmex-XN haematology analyser (Sysmex UK Limited, Milton Keynes, UK) to generate an extended profile of blood cell indices. Full blood count results were reviewed by NHSBT staff to identify clinically significant results for further consideration. As the STRIDES BioResource is part of the NIHR BioResource, consenting donors have also joined the NIHR BioResource Research Tissue Bank (REC: 17/EE/0025) (https://bioresource.nihr.ac.uk/), providing opportunities for participation in additional research projects, subject to provision of further study-specific consent.

## Statistical methods

### Statistical methods for primary and secondary outcomes {20a}

#### Principles

Intention-to-treat analyses will be used. Principal analyses will concern the assessment of the main effects of interventions based on outcomes aggregated at the site level (i.e. unit of randomisation). Tests of interaction will assess whether results differ between pre-specified subgroups. Subsidiary analyses will be done using individual-level data with allowance for clustering of observations by site. Multiple testing will be taken into account when interpreting results other than the principal analyses. The trial will be reported according to CONSORT guidelines.

#### End-of-trial analyses

Primary analyses will calculate odds ratios for the main effects of interventions using a binomial generalised linear mixed model fitted to the aggregate number of primary outcomes recorded in each 9-month period by site with the denominator as the number of donations recorded by site-period (defined by NHSBT as a complete donation or a partial donation). Adjustments will be made for the baseline prognostic variables considered for balancing at randomisation (i.e. historical VVR rates, total numbers of donors bled, and type of site), plus dummy variables for the four nine-month periods of intervention, and a random effect for the site. Key secondary analyses related to the primary outcome will include an assessment of interactions of interventions and possible variation of the main effects by period and baseline characteristics. Analyses of other secondary outcomes will follow the same approach as for the primary outcome.

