## Introduction

### Background and rationale

Vasovagal reactions (VVRs), the most common acute complication related to blood donation, are responsible for substantial morbidity, especially when accompanied by complications such as fall and fractures [1–3]. VVRs also discourage individuals to donate again, reducing the likelihood of repeated donations by more than 50% [4, 5]. Furthermore, VVRs can disrupt the throughput and yield of donor sessions due to social contagion “ripple effects” on other donors attending the same sessions [6]. VVRs are not only harmful for donors but also costly and highly disruptive for blood services.

Operating at different stages of blood donation, the principal mechanisms believed to underlie donation-related VVRs include the direct effects of removal of ~500mL of blood; the stress of giving blood (e.g. fear of needles, pain, sight of blood); and orthostatic effects superimposed on a relative hypovolaemic state after donation [7, 8]. Based on this understanding, various strategies to prevent VVRs have been proposed. For example, the World Health Organisation (WHO) recommends pre-donation hydration and applied muscle tension (AMT), a technique to increase blood flow and blood pressure by tensing and releasing muscles. The EU Domaine Project, which also endorses the use of pre-donation hydration and AMT, additionally recommends caffeine loading, distraction techniques, supportive care, and educational material [9–11]. Blood services worldwide have adopted varying strategies to prevent VVRs; water loading and AMT are the most common [12–15].

A previous meta-analysis of randomised trials has, however, shown that there is limited evidence to support water loading or AMT [16–18], because previous studies have typically involved small sample sizes; non-representative populations; non-robust outcomes definitions; and sub-optimal randomisation methods. These concerns apply even more sharply to the sparser evidence available on other interventions used by some blood services, including isotonic drinks [19–21] prolongation of post-donation recovery time, and psychosocial educational materials [22, 23]. Hence, blood services need more robust evidence to help shape and inform their currently diverse approaches to prevent VVRs.

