#### Main trial design

STRIDES is a cluster-randomised cross-over/stepped-wedge factorial trial of four interventions to reduce VVRs involving randomisation of all 73 blood donation sites (mobile teams and donor centres) of NHSBT in England. Four interventions were compared to current practice in NHSBT (i.e. *vs* standard of care as reference): (i) 500-ml isotonic drink before donation (*vs* current 500-ml plain water); (ii) 3-min rest on donation chair after donation (*vs* current 2 min); (iii) new modified AMT (*vs* current practice of AMT); and (iv) psychosocial intervention using preparatory materials (*vs* current practice of nothing). Each blood donation site (i.e. “cluster”) has been randomly allocated to receive one or more interventions during four 9-month periods (i.e. a 36-month total period) using principles of cross-over (for isotonic drink and time spent in donation chair, to reduce between-cluster confounding and maximise statistical power), stepped-wedge (for the modified AMT and psychosocial interventions, since these interventions cannot be “un-learned” by participants once introduced to the trial) and factorial trial design to construct the temporal sequence of interventions (Supplementary Table 1). A cluster randomised trial design was preferred as it was most practicable for service-wide adoption without disrupting routine blood donation and minimised contamination across interventions.

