### Criteria for discontinuing or modifying allocated interventions {11b}

As this pragmatic trial was embedded into routine donation services, the study has been open to the following minor amendments. First, if a participant has not wished to receive the trial’s interventions, they have been able to receive NHSBT’s standard interventions (e.g. water loading rather than the isotonic drink evaluated in the trial). Second, the trial has been conducted during the COVID-19 pandemic, meaning that during the study NHSBT has routinely implemented service-wide revisions with the aim of enhancing donor and staff safety at donation sessions, including limiting the number of donors per session and removing hot drinks previously offered after donations.

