### Sample size {14}

The trial sample size has been informed by (i) the need to generate evidence sufficiently compelling to influence regulators and policy-makers; (ii) NHSBT's duty of care to 900,000 blood donors per year, making it vital for the service to evaluate even small changes in VVR rates; (iii) NHSBT’s objective to optimise blood collection procedures, improve donor return rates, and improve donor (and staff) well-being and satisfaction; and (iv) the need for appropriate power to study determinants of VVRs, both singly and in combination.

Power calculations have been based on the primary endpoint (defined above), assuming a 5% type I error probability and service-wide cluster randomisation (involving 73 teams with ~15,000 whole blood donations per 9-month period per team, and overall primary outcome rate of 0.18% per donation). For the two interventions being assessed using a cross-over design (i.e. isotonic drink and time on donation chair after donation), there is >90% power to detect an odds reduction of >8% (odds ratio of 0.92). For the two interventions being assessed using a stepped-wedge design (i.e. modified AMT and psychosocial intervention), there is >90% power to detect an odds reduction of >13% (odds ratio of 0.87) (Fig. 2). Hence, the study is powered to detect smaller odds reductions than previously reported in the literature but still of importance to blood services. For example, a 10% risk reduction would prevent ~300 severe VVRs per year in NHSBT. All interventions have been tested versus current practice with a 5% overall family-wise error rate control.

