**Fig. 2 Fig2:**
[figure not shown]
Statistical power of the trial. Calculated for the two interventions in the study were assessed using a cross-over design (i.e. isotonic hydration and time on donation chair after donation; red line) and the two interventions in the study were assessed using a stepped-wedge design (i.e. modified AMT (applied muscle tension) and psychosocial intervention; blue line). Each intervention was tested at a Bonferroni corrected level (type I error) of 0.0125. The study design has four possible sequences for interventions assessed using a stepped-wedge design (X-I-I-I, X-X-I-I, X-X-X-I, X-X-X-X), and two possible sequences for interventions assessed using a cross-over design (X-I-X-I, I-X-I-X) with a study duration of 3 years and each period lasting 9 months (X = current practice, I = intervention). Power calculations assume 15,000 whole blood donations per 9-month period in each donation centre, with an overall rate of severe (syncope) VVRs of 0.18% per donation and a between-centre variance in log odds of 0.06 (estimated from 2014/15 NHSBT data)

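### The primary model allows for stable site differences but not for site-specific change between periods; unless that variation is zero, all four standard errors are too small and the 5% family-wise error rate is exceeded

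*Protocol article*

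**What the plan says.** The section on end-of-trial analyses estimates the main effects "using a binomial generalised linear mixed model fitted to the aggregate number of primary outcomes recorded in each 9-month period by site". The denominator is the number of donations in the site-period. The model adjusts for the three baseline balancing variables and includes "dummy variables for the four nine-month periods of intervention, and a random effect for the site". The other secondary outcomes follow the same approach.

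No other section covers site-specific change over time. The planned look at variation of main effects by period is a treatment-by-period interaction in a secondary analysis. The individual-level analyses account for clustering at site level.

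On error control, the sample size section says: "All interventions have been tested versus current practice with a 5% overall family-wise error rate control". The Fig. 2 caption gives the per-test level: "Each intervention was tested at a Bonferroni corrected level (type I error) of 0.0125". The only clustering input listed for the power calculation is "a between-centre variance in log odds of 0.06 (estimated from 2014/15 NHSBT data").

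**The concern.** In the sequences X-I-X-I and I-X-I-X each site is its own control. A constant site effect cancels from that contrast, so its standard error depends on how much a site's log-odds varies between periods. The stated model lets that variation come from two sources only: a period shift common to all sites, and binomial sampling. The stepped-wedge comparisons use some between-site information, but most of theirs is also within-site.

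The document gives reasons to doubt that nothing else varies:

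- The background says that "VVRs can disrupt the throughput and yield of donor sessions due to social contagion", which suggests that outcomes within a session are not independent.
- The Fig. 1 caption says that mobile teams collect at changing locations within their area.
- The trial runs for 36 months through the pandemic, and sites may have been affected unevenly.

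If such variation exists, confidence intervals for all four interventions are too narrow and p-values too small, in a trial whose results are meant to inform national donation policy directly.

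**Working it through.** **Inputs from the document.** 73 sites ("randomisation of all 73 blood donation sites"); 4 periods, so 73 × 4 = 292 cells; 15,000 donations per cell; event rate 0.18%; between-centre variance 0.06; per-test level 0.0125; odds ratios 0.92 (cross-over) and 0.87 (stepped-wedge); sequences as in the Fig. 2 caption.

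**Assumptions.** Tests are two-sided (sidedness is not stated). Sites are split equally over sequences. The site-by-period variance w is not in the document; the values 0, 0.003, 0.006 and 0.012 are used, that is 0%, 5%, 10% and 20% of 0.06.

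**1. Sampling variance per cell.** Expected events are 15,000 × 0.0018 = 27. On the log-odds scale the variance is 1/(15,000 × 0.0018 × 0.9982) = 0.0371.

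**2. Standard errors under the stated model (w = 0).** For the cross-over the site variance drops out: SE = √(4 × 0.0371/292) = 0.0225. For the stepped-wedge, generalised least squares with period effects and site variance 0.06 gives SE = 0.0379.

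**3. The stated power.** Power = Φ(|ln OR|/SE − 2.498), where 2.498 is the two-sided critical value at 0.0125.

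- Cross-over: |ln 0.92| = 0.0834; 0.0834/0.0225 ≈ 3.70; power 88.5%. The odds ratio detectable with 90% power is 0.918.
- Stepped-wedge: |ln 0.87| = 0.1393; 0.1393/0.0379 ≈ 3.68; power 88.1%. The odds ratio detectable with 90% power is 0.867.

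Both detectable odds ratios round to the stated 0.92 and 0.87. The claim of more than 90% is thus reproduced approximately, through rounding, with w set to zero.

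**4. Effect of w > 0 on the stated model.** For the cross-over the true SE is √(4 × (0.0371 + w)/292), while the model still reports 0.0225. For the stepped-wedge the true SE is the sandwich SE of the same estimator. The per-test error is 2 × [1 − Φ(2.498 × model SE/true SE)]. The family-wise error is 1 − (1 − a)²(1 − b)², where a and b are the per-test errors for cross-over and stepped-wedge and the four tests are treated as independent.

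| w | True/model SE, cross-over | True/model SE, stepped-wedge | Per-test error, cross-over | Per-test error, stepped-wedge | Family-wise error |
|---|---|---|---|---|---|
| 0 | 1.00 | 1.00 | 1.25% | 1.25% | 4.9% |
| 0.003 | 1.04 | 1.04 | 1.63% | 1.59% | 6.3% |
| 0.006 | 1.08 | 1.07 | 2.05% | 1.96% | 7.8% |
| 0.012 | 1.15 | 1.14 | 2.99% | 2.79% | 11.1% |

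**5. Simulation check.** Factorial trials of 73 sites with no intervention effects were simulated and fitted by maximum likelihood with the stated random-site model (no baseline covariates). The family-wise error was 5.1% at w = 0, 6.4% at 0.003 and 8.7% at 0.006, slightly above the analytic values. At larger assumed values it was 10.8% (w = 0.01) and 17.9% (w = 0.02).

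**6. With the variation allowed for.** A site fixed-effect linear model on empirical logits, with the residual variance estimated, gave a simulated family-wise error of 4.7% to 5.3% for w from 0 to 0.02. Power with w in the model, at 0.0125:

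| w | Cross-over, OR 0.92 | Stepped-wedge, OR 0.87 |
|---|---|---|
| 0 | 88.5% | 88.1% |
| 0.003 | 85.5% | 85.4% |
| 0.006 | 82.5% | 82.7% |
| 0.012 | 76.3% | 77.3% |

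**The case against.** The strongest objection is that the consequence depends on a quantity the document does not report. A reader might infer that the standard errors are certainly too small and that family-wise control has failed. The document does not support that: at w = 0 the stated model holds its level (4.9% analytic, 5.1% simulated). This objection stands, and the point is conditional for that reason.

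The pandemic changes, such as "limiting the number of donors per session and removing hot drinks previously offered after donations", might also be read as direct evidence of site-by-period variation. They are not. The protocol describes them as service-wide, and the period dummies absorb a shift common to all sites. Only uneven responses between sites would add to w, and none are reported. The contagion argument is likewise indirect. It concerns vasovagal reactions in general and gives no size for loss-of-consciousness events once about 15,000 donations are pooled in a cell.

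Setting the reduced power figures against the stated 90% would overstate the loss, because the starting point is about 88%. The loss due to this term is about 3 points at w = 0.003 and 5 to 6 points at 0.006. Nor does the caption show how the 2014/15 data were used, so one cannot conclude that time-varying site variance could not have been separated there.

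Finally, a condensed article may leave dispersion checks to an analysis plan that is not shown. That is fair for checks. But the article does state the random part of the primary model, and what it states makes no allowance for this variation.

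**Conclusion.** The concern holds in conditional form. The stated primary model is valid only if site-by-period variance is exactly zero. Any positive value makes the standard errors too small for all four interventions and takes the family-wise error above 5%. Little is needed: w = 0.003 adds about 8% to the cell sampling variance (0.003/0.0371) and takes the family-wise error to about 6.3%. The figures of 7.8% and 11% at 0.006 and 0.012 rest on assumed variances, two-sided tests, equal allocation to sequences and the planning values for volume and event rate. Positive variation is plausible on the document's own account but is not quantified there. The stated power rests on the same zero and, even then, reaches 90% only through rounding of the odds ratios.

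**What to change.** In the section on end-of-trial analyses, extend the random part to a random effect for site plus a random site-by-period effect, one per analysed site-period cell. Apply this to the primary outcome and to the secondary outcomes that follow the same approach. An equivalent allowance at site-period level would also serve, such as an overdispersion term or a cluster-robust variance with a small-sample correction. Whichever is chosen should be named before the analysis is run.

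Restate the Fig. 2 power over a range of assumed site-by-period variances beside the 0.06, including zero. Since the recruitment window is fixed, this does not change the sample size; it shows readers what the stated power assumes.

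The cost is one line of text and one variance parameter, estimated from 292 cells in 73 sites. Intervals widen slightly if the variance is positive. Because the estimate cannot fall below zero, it will sometimes be positive by chance, so intervals may widen a little even when the true variance is zero.

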#### Secondary outcomes

Secondary outcomes are (i) all in-session VVRs (i.e. with and without loss of consciousness); (ii) all delayed VVRs (i.e. VVRs with and without loss of consciousness after leaving the donation venue); (iii) delayed VVRs with loss of consciousness; and (iv) any in-session non-VVR adverse events or reactions, such as bruising and rebleeds.

All outcomes will be assessed at the end of the trial and will involve comparison of event rates in periods with and without interventions applied (Appendix 1). The data on the primary and secondary outcomes will be complete by design, as the recording of on-session adverse events, including VVRs, is mandatory in the blood service.

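### In-session non-VVR events are adjusted for sites' VVR history without their own pre-trial rate, which may cost the AMT and psychosocial odds ratios a little precision

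*Protocol article*

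**What the plan says.** Under End-of-trial analyses in {20a}, the primary model is a binomial mixed model on site-period counts. It adjusts for the variables balanced at randomisation, "historical VVR rates, total numbers of donors bled, and type of site", with period dummies "and a random effect for the site". The same paragraph then extends this to the rest: "Analyses of other secondary outcomes will follow the same approach as for the primary outcome". No outcome-specific baseline rate is named.

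Secondary outcomes in {12} lists four outcomes. Three are VVR outcomes: (i) all in-session VVRs, (ii) all delayed VVRs, and (iii) "delayed VVRs with loss of consciousness". The fourth is different in kind: "any in-session non-VVR adverse events or reactions, such as bruising and rebleeds". The same section says that "the recording of on-session adverse events, including VVRs, is mandatory in the blood service".

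**The concern.** A site's past VVR rate need not say much about its past rate of bruising and rebleeds. The natural site-level predictor of outcome (iv) is the site's own history of those events, and the blood service probably holds it.

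How much this matters differs by intervention. The drink and chair contrasts are made within sites, so the between-site variance left in the model does not affect them. The AMT and psychosocial contrasts come from a stepped wedge and borrow some information from comparisons between sites. The weight of that information depends on the unexplained site variance. Predictable site variance left in the model therefore widens the AMT and psychosocial intervals for outcome (iv), the only listed outcome that captures non-VVR harm.

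**Working it through.** **Inputs from the article** (Sample size {14} and the Fig. 2 legend): 73 sites; 15,000 donations per site-period; primary rate 0.18%; site log-odds variance τ² = 0.06; α = 0.0125 per intervention; cross-over sequences X-I-X-I and I-X-I-X; stepped-wedge sequences X-I-I-I, X-X-I-I, X-X-X-I and X-X-X-X.

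**Assumed, because the article does not give them:**
- a two-sided test and sites split equally over sequences;
- for outcome (iv), a rate of 0.1% to 1% and the same τ² = 0.06 (given for the primary outcome only);
- a history of one pre-trial year, 15,000 × 12/9 = 20,000 donations per site;
- the share k of a site's underlying log-odds variance that persists into the trial.

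**Step 1: reproduce the plan's power.** Generalised least squares on site-period log-odds, with four period dummies plus treatment, cell variance 1/(15,000·p·(1−p)) and site variance 0.06. Power = Φ(|ln OR|/SE − z), with z at 1 − 0.0125/2.
- Cross-over: SE 0.0225, power 88.5% at OR 0.92; OR detectable with 90% power 0.918.
- Stepped wedge: SE 0.0379, power 88.1% at OR 0.87; OR detectable with 90% power 0.867.

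The detectable odds ratios round to the stated 0.92 and 0.87, so the model is a fair stand-in for the plan's own calculation.

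**Step 2: how much can any site-level covariate gain?** At the primary outcome's inputs, discarding all between-site information raises the stepped-wedge SE only from 0.0379 to 0.0403. Most of the information is already within sites.

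**Step 3: the gain from own history for outcome (iv).** All four interventions are in the model, averaged over 60 random allocations, with cell variance 1/(15,000·p).
- Reliability of the history: 0.06/(0.06 + 1/(20,000·p)).
- Extra site variance explained: R² = k × reliability.
- Residual site variance: 0.06 × (1 − R²).

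| Rate p | Reliability | SE, no own history | SE, k = 1 | Cut, k = 1 | Cut, k = 0.80 | Cut, k = 0.64 |
|---|---|---|---|---|---|---|
| 0.1% | 0.06/(0.06+0.05) = 0.55 | 0.0492 | 0.0462 | 6.1% | 4.4% | 3.2% |
| 0.3% | 0.06/(0.06+0.0167) = 0.78 | 0.0301 | 0.0275 | 8.7% | 4.9% | 3.2% |
| 1% | 0.06/(0.06+0.005) = 0.92 | 0.0170 | 0.0153 | about 10% | about 3.3% | 1.8% |

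Cuts are from unrounded SEs. The k = 0.64 column is a correlation of 0.8 between past and trial-period site effects (0.8² = 0.64). The whole table assumes that the existing covariates explain none of the site variance in outcome (iv).

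**Step 4: sensitivity.**
- If the existing covariates already explain 25% and own history subsumes them, the cut at k = 0.64 is 1.1% to 2.1%, and at k = 1 it is 4% to 10%.
- At a rate of 0.03%, one year of history has reliability 0.26 and the cut is at most about 2.5%.
- Site-by-period variance of 0.01 to 0.02, with uninformative existing covariates, gives 3.7% to 4.8% at k = 0.80 and 5.0% to 8.1% at k = 1.
- Pooling three years (60,000 donations, assumed) raises the ceiling to 11.8% to 17.7%, but again only with k = 1 and uninformative existing covariates.
- The cross-over SE changes by no more than 0.05% in the Step 3 runs.

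**The case against.** The strongest objection is that nothing in the plan is invalid. Adjusting for the variables used in the restricted randomisation ({16a}) is sound, the random site effect already carries most of the load, and outcome-specific covariates are often left to an analysis plan, which is not shown here. This stands as a limit on severity. It does not remove the point, because the article states a covariate set and then extends it to the secondary outcomes.

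A reader might infer that every secondary outcome is adjusted for the wrong history. The documents do not support that. For "all in-session VVRs (i.e. with and without loss of consciousness", the historical VVR rate is its own history or close to it. For delayed VVRs, no usable pre-trial series is shown to exist: mandatory recording is stated only for on-session events, and {18a} has donors prompted by text message to phone in adverse events.

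A reader might also take 6% to 10% as the expected loss. That needs perfectly persistent site rates, and {11b} describes service-wide COVID-19 changes, including limits on donors per session, which make perfect persistence doubtful. It also needs the three retained covariates to explain nothing.

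Finally, the event rate, site variance and persistence for outcome (iv) are not in the article, so no loss is demonstrated for this trial. That is correct; the sizes given are ranges under stated assumptions.

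**Conclusion.** The point holds as a minor efficiency improvement for one outcome, in-session non-VVR events, and for two of the four interventions, modified AMT and the psychosocial materials. There is no bias, no invalid test and no effect on the primary-outcome analysis or the cross-over contrasts. With one year of history, a site variance of 0.06 and rates of 0.1% to 1%, the stepped-wedge SE would fall by about 1% to 5% at 64% to 80% persistence. The 6% to 10% figure is a best case for one year of history. The gain shrinks further for very rare events. The direction is secure; the size rests on inputs that the article does not give.

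**What to change.** State in {20a} that the model for in-session non-VVR events keeps the three balancing covariates and adds the site's pre-trial rate of those same events (on the log-odds scale), pooled over the years available. Do the same for delayed VVRs only if a reliable pre-trial site-level series exists; otherwise keep the current covariates. The new covariate is an addition and should not replace the historical VVR rate.

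The cost is one sentence, one extract of historical site-level counts and one degree of freedom per model. That the extract can be had is an assumption, based on the mandatory recording of on-session events. No donor contact or new data collection is needed.
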